### Rationale

NBP was originally extracted from the seeds of Apium Graveolens Linn. It is an effective ingredient of Chinese herbal medicine that used to treat epilepsy [11]. However, it has been found that the effective dose and the toxic dose in treating epilepsy are close, which has a greater safety risk. Therefore, the focus of research has shifted from epilepsy to stroke. Subsequent studies have shown that in the rat ischemic stroke model, NBP can reduce infarct volume, neuronal cell death and brain edema, and preserve the blood–brain barrier [11–17]. A study compared the incidence of stroke, the volume of the brain lesion, patency of the microvessels by FITC-dextran perfusion and the number of microvessels by immunohisochemical detection of vwF between NBP pretreatment group and control group. The incidence of ischemic stroke and the volume of the infarct were decreased, and the perfused microvessels were increased with NBP pretreatment [18]. In addition, NBP reduced glial fibrillary acidic protein (GFAP)-positive astrocytes induced by chronic cerebral ischemia, so as to play a protective effect on hippocampal injury [19]. NBP plays a role in different pathophysiological processes in the treatment of ischemic stroke, including antioxidants, anti-inflammatory, anti-apoptotic, anti-thrombosis, and mitochondrial protection [4, 20]. A study showed that NBP could display strong activity in inhibiting the arachidonic acid (AA)- and adenosine diphosphate (ADP)-induced platelet aggregation in vitro. Furthermore, NBP could release moderate levels of NO and H2S, which would be beneficial in improving cardiovascular and cerebral circulation [21]. Butylphthalide also increases vasodilation and inhibits platelet aggregation [22]. NBP has been confirmed to increases VEGF expression and decreases poststroke inflammation and MMP-9 expression in animal models of stroke [23, 24]. In view of its powerful therapeutic effect on ischemic stroke in animal models, the State Food and Drug Administration of China approved it for clinical trials. The Phase IV clinical research trial was completed in February 2005. NIHSS, Barthel index (BI) and Activities of Daily living scale (ADL) were used as the end points of the study. Total effective rate = (Basic recovery cases + significant improvement cases)^a^ / total number of cases × 100%. And the total effective rate of butylphthalide was 78.2% [25, 26]. A research investigated the effects of dl-3-n-butylphthalide (NBP) on the level of circulating endothelial progenitor cells (EPCs) and clinical outcome in patients with acute ischemic stroke (AIS).The results showed that the levels of circulating EPCs on days 14 and 30 were significantly higher in the NBP group than in the control group. In contrast, NIHSS score was notably lower in NBP group on day 14, 30 and day 90. The mRS score in the NBP group was lower on day 90 [27].

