### Explanation for the choice of comparators {6b}

Doctors will make medication plans for secondary prevention according to their parents’ condition when they are discharged, and recommend (rather than forcing) them to take butylphthalide. We will manage patients through Internet means such as WeChat Mini Programs, and record their medication regularly. At the end of the whole study cycle, we will take patients who take NBP for 3 months as NBP group, and patients who refused to take butylphthalide or poor drug compliance^b^ as the control group. In addition, we will faithfully record other drugs except butylphthalide soft capsules.

*b:According to the formula: “medication compliance* = *actual number of tablets / number of tablets to be taken* × *100%”, we calculate the patient’s drug compliance. 80% to 120% will be considered as good compliance, while* < *80% or* > *120% will be considered poor compliance.*

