## Objectives {7}

The objective of this trial is to confirm the efficacy and safety of butylphthalide on secondary prevention of stroke patients through follow-up of the experimental group and the control group. It provides clinical evidence for NBP to prevent and treat stroke, and has certain significance for improving treatment and prognosis of patients.

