**Fig. 1 Fig1:**
[figure not shown]
The flow chart of the trial. *: According to formula: “medication complianece = actual number of tablets / nunmber of tablets to be taken × 100%”, we calculate the patient's drug compliance. 80% to 120% will be considered as good compliance, while < 80% or > 120% will be considered poor compliance

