##### Adverse events

Adverse events include emerging clinical cardiovascular events within one year (sudden death/ myocardial infarction/ arrhythmia/ heart failure, etc.), and other adverse reactions of patients in the trial group. During the follow-up period, we will add tests for other adverse reactions such as liver and kidney function, bleeding and blood coagulation.

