#### Unblinding and allocation

At the end of the study cycle, the researchers will reveal the actual medication information of the patients, taking patients with good butylphthalide compliance as the butylphthalide group, and patients without taking butylphthalide and patients with poor compliance as the control group, and compare the difference of outcomes between the two groups.

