## Statistical methods

### Statistical methods for primary and secondary outcomes {20a}

The Kaplan–Meier method is used to draw the survival analysis curve of the percentage of patients with recurrent stroke within 1 month, 3 months, 6 months and 1 year of follow-up. The LogRank method is used to compare the statistical difference in the survival curve between the two groups. The COX proportional regression model is used to calculate the risk ratio (hazards ratios) and 95% CI.

The measurement data (such as NIHSS score and modified Rankin score) is expressed by x ± s, and t-test or Wilcoxon rank sum test is used for comparison between groups. The counting data (such as clinical efficacy and adverse reactions of the two groups) is expressed by chi-square test or Fisher exact test. The subgroup analysis is carried out according to sex, age, medical history and type of stroke.Propensity score matching (PSM) is taken to ensure that the covariates are balanced and comparable. A two-sided *P* value of 0.05 or less is considered statistically significant. All the analyses are done with SPSS software 18.0 or based on R software 3.4.3.

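### Patients who take more than 120% of their planned butylphthalide are analysed in the control group, which biases the safety comparison in favour of the drug

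*Protocol article*

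**What the plan says.** The section on the choice of comparators {6b} defines compliance as the number of tablets taken divided by the number due. In the words of the Fig. 1 legend, "80% to 120% will be considered as good compliance". Anything below 80% or above "120% will be considered poor compliance".

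The same section makes up the control group from "patients who refused to take butylphthalide or poor drug compliance". The section on unblinding and allocation repeats this for the end of the study. There, good compliers form the butylphthalide group, "patients without taking butylphthalide and patients with poor compliance as the control group", and outcomes are compared between the two.

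Safety is part of the stated aim, "to confirm the efficacy and safety of butylphthalide on secondary prevention of stroke patients" (Objectives {7}). The abstract lists adverse events by group as a secondary outcome. Statistical methods {20a} applies a chi-square or Fisher exact test to count data such as "clinical efficacy and adverse reactions of the two groups". The adverse-event definition under Outcomes {12} covers cardiovascular events and "other adverse reactions of patients in the trial group".

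The planned dose is 0.2 g three times daily (Intervention description {11a}). The item on handling non-adherence {20c} is marked as not applicable.

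**The concern.** An upper compliance limit of 120% is commonly used to exclude patients from a per-protocol set. Here the patient is not excluded but relabelled. Someone who took more butylphthalide than prescribed is analysed in a group whose stated treatment is routine care without butylphthalide.

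For safety this puts exposed patients on the wrong side of the comparison. If the drug causes reactions, the control rate rises. If reactions also become more frequent with intake, the butylphthalide rate falls below the rate among all takers. Both errors shrink the apparent excess of reactions on butylphthalide, and safety is a declared objective of the trial.

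**Working it through.** **Who is moved.** The planned dose is 3 × 0.2 g = 0.6 g/d. The limit is 1.2 × 0.6 g = 0.72 g/d on average, when tablets taken and tablets due cover the same period. Intake between 100% and 120% stays in the butylphthalide group.

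**Where the reactions go.** Two readings are possible.
- Abstract, unblinding and allocation, and {20a}: reactions are compared between the compliance-defined groups, so over-takers' reactions enter the control rate.
- Adverse-event definition under Outcomes {12}: non-cardiovascular reactions are those of the trial group, which over-takers have left. Their reactions then vanish from the butylphthalide profile. The count falls in any case. The rate falls if over-takers react more often than compliers.

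**The plan's own figure.** 17.7% versus 14.7%, two-sided alpha 0.05, 90% power, pooled variance, no continuity correction: 3168 per group, as stated in Sample size {14}. 3168/0.85 = 3727.06, stated as 3727. This point does not depend on that figure.

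**Size under the first reading.** The protocol gives no share of over-takers and no reaction rates, so all of these are assumptions: reaction rates of 2% in controls and 4% in compliant takers; *f* = share of takers above 120%; *r* = over-taker rate divided by complier rate; equal numbers of takers and non-takers; no takers below 80%, so that the effect of the upper limit is isolated.

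- By actual intake: RD = 4% × (1 − f + f·r) − 2%
- As the protocol groups them: RD = 4% − (2% + f·r·4%)/(1 + f)

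| f | r | by intake (points) | as analysed (points) | fall (points) |
|---|---|---|---|---|
| 1% | 1 | 2.00 | 1.98 | 0.02 |
| 1% | 2 | 2.04 | 1.94 | 0.10 |
| 1% | 3 | 2.08 | 1.90 | 0.18 |
| 5% | 1 | 2.00 | 1.90 | 0.10 |
| 5% | 2 | 2.20 | 1.71 | 0.49 |
| 5% | 3 | 2.40 | 1.52 | 0.88 |

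Example for f = 5%, r = 2: by intake 4 × (0.95 + 0.10) − 2 = 2.20; as analysed 4 − (2 + 0.05 × 2 × 4)/1.05 = 4 − 2.29 = 1.71.

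**Size under the second reading.** The share of all takers' reactions that is lost is f·r/(1 − f + f·r). For r = 1, 2, 3 this is 1.0%, 2.0%, 2.9% at f = 1%, and 5.0%, 9.5%, 13.6% at f = 5%.

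**Recurrence.** Take 8000 × 0.85/2 = 3400 evaluable per group by actual intake (equal split assumed), and give over-takers the 14.7% rate. The control rate becomes (17.7% + f × 14.7%)/(1 + f), with group sizes 3400(1 + f) and 3400(1 − f). Unpooled two-proportion z test, two-sided 0.05:
- f = 0: difference 3.00 points, power 91.9%
- f = 1%: 2.97 points, 91.4%
- f = 5%: 2.86 points, 89.4%

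**The case against.** The best defence has three parts.

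**Over-takers may be very few.** This stands. Nothing in the protocol says how many there will be, and at 1% the loss is a fraction of a point.

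**A safety population is often left to the analysis plan.** This stands only in part. A separate safety set may exist in a document not shown. But the protocol itself fixes the grouping rule, applies it to outcomes in general, and tests adverse reactions between the two groups. That is a stated rule, not an omission.

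**The groups might follow patients' own choice, as the abstract and Trial design {8} say, or a patient who took the drug for 3 months might qualify whatever the amount.** This does not stand. The comparator section sends poor compliers to the control group, and the section on unblinding and allocation limits the butylphthalide group to good compliers.

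Some stronger readings are tempting but not supported:
- *Any intake above plan makes a patient a control.* Only intake above 120% does.
- *Long-term users become controls, for example after day 108 (90 × 1.2).* This needs a fixed 90-day denominator that the protocol does not state. The adherence section {11c} divides by the total planned for the individual participant, so a longer plan taken in full scores about 100%.
- *The protocol itself shows that excess intake is close to toxic.* The Rationale says that "the effective dose and the toxic dose in treating epilepsy are close, which has a greater safety risk". That concerns another indication and gives no dose, so it says nothing about modest excess over 0.6 g/d after stroke.

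**Conclusion.** The rule is wrong as written: patients exposed above the planned dose are analysed as unexposed. If butylphthalide causes reactions, the direction of the error favours it. Under the reading that drops their reactions, the rate itself is affected only if reactions rise with intake.

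The size cannot be known from the protocol. On the assumed rates of 2% and 4%, moving 1% of takers lowers the risk difference by about 0.02 to 0.18 points. A reader might take the 5% rows as the expected loss: 22% (2.20 to 1.71) or 37% (2.40 to 1.52). The documents do not support that. Those rows need both a 5% share of over-takers and a doubled or tripled reaction rate. Measured against the 2.00-point excess at the planned dose, the same analysed values are falls of 14% and 24%. The effect on the recurrence comparison is small.

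Confidence is high about the rule and its direction, and low about its magnitude. The correction is worth making because it costs almost nothing. Placing patients below 80% in the control group for efficacy is a separate and probably larger problem, which this point does not settle.

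**What to change.** - In the comparator section {6b}, the Fig. 1 legend, and the section on unblinding and allocation, state that intake above 120% never moves a patient to the control group.
- In the adverse-event definition and Statistical methods {20a}, compare adverse reactions by actual exposure. Anyone who took butylphthalide counts as exposed, whatever the compliance, and the amount taken is recorded. For safety this also covers takers below 80%, whose reactions would otherwise still be counted as control reactions.

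The cost is protocol wording and a changed derivation from medication data that the diary and the Mini Program forms already collect. No extra patients or visits are needed. Groups are formed only at the end of the study, so the change can be made before analysis.

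The downside is a butylphthalide group more mixed in dose, which the recorded exposure can describe. The change does not resolve the efficacy grouping of patients below 80%.

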## Objectives {7}

The objective of this trial is to confirm the efficacy and safety of butylphthalide on secondary prevention of stroke patients through follow-up of the experimental group and the control group. It provides clinical evidence for NBP to prevent and treat stroke, and has certain significance for improving treatment and prognosis of patients.

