NBP has been widely used for treating acute ischemic stroke in China and shows a great clinical effect [4]. According to the Chinese Guidelines for Evaluation and Intervention of Collateral circulation in Ischemic Stroke 2017, interventions for collateral circulation include non-drug interventions, such as external counterpulsation (IIb recommendation, Grade C evidence); and drug interventions, such as NBP (IIa recommendation, Level B evidence) [5]. According to a meta-analysis in 2019, researchers found evidence that the combination of NBP and conventional neuroprotective agents can improve functional recovery 90 days after ischemic stroke compared with traditional drugs alone [6]. NBP is a safe and effective treatment for progressive cerebral infarction (PCI). A randomized, double-blind, controlled study was conducted on the effectiveness and safety of NBP in the treatment of PCI (Zhang et al., 2017). The primary endpoints were the National Institutes of Health Stroke Scale (NIHSS) score before treatment and at 7, 14, 21, and 30 days after treatment, and Barthel Index (BI) evaluation on the 90th day of treatment. The result shows that NBP can improve the prognosis and reduce the burden of daily life of PCI patients [7]. Other randomized, double-blind, placebo-controlled, multicenter clinical trials suggest that NBP may be a safe and effective treatment for ischemic stroke [8–10]. In addition, a Phase II clinical trial of NBP soft capsules for patients with ischemic stroke began in the United States in 2017 (NCT02905565) [5]. To sum up, the current research is mainly focused on the short-term treatment of stroke patients with RCT. Therefore, we designed this study to confirm the role of butylphthalide in secondary stroke prevention in the real world.

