## Trial design {8}

This study is an open-label, noninferiority, two-armed, prospective, multicenter, real world trial conducted at Northwest University in Xi’an, China. The participants will be recruited from 78 hospitals across mainland China. Eligible participants will be assigned to the butylphthalide group or the control group according to their own wills. Every researcher at each study center is scheduled to recruit patients from December 2020 to June 2023. The flow chart of the trial is shown in Fig. 1.

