## Assignment of interventions: allocation

### Sequence generation {16a}

This study is a real-world trial, with subjects assigned to this trial based on their actual conditions and wishes.

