### Real world research settings

#### Intervention measures

In order to better reflect the efficacy of butylphthalide soft capsules in the real world, doctors will make medication plans for secondary prevention according to their condition when they are discharged, and recommend (rather than forcing) patients to take butylphthalide. The researchers will not take other interventions for the secondary prevention of patients.

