## Discussion

A systematic review found evidence suggesting that the combination of NBP and conventional neuroprotective agents improves functional recovery at 90 days after ischemic stroke compared with conventional drugs alone [6]. And many randomized, double-blind, placebo-controlled, multicenter clinical trials also suggest that NBP may be a safe and effective treatment for ischemic stroke [7–10]. This trial will be exploring the efficacy and safety of butylphthalide in secondary prevention of ischemic stroke, in order to expand the application of butylphthalide soft capsules and provide new evidence for enriching the secondary prevention of stroke.

In addition, this trial is a real-world trial highlighting the practicability of the research results. We have a larger sample size and a longer follow-up time, which can better reduce the sampling error and more easily detect other adverse events. This research can better represent the target population, and its treatment methods are close to the actual treatment [31], which can better reflect the effectiveness of butylphthalide in the real world.

The most important feature of this study is to use the network platform to complete the follow-up. In previous studies, it is difficult for patients to complete NIHSS score or mRS score in follow-up by returning to the hospital, resulting in a large number of dropouts and incomplete information. In this study, researchers score the mRS and NIHSS of the subjects by making a video call with them. So it could eliminate the inconvenience of patients returning to hospital for follow-up. In addition, by Wechat group, Wechat Mini Programs and other ways, we could manage patients, remind patients of medication time, guide patients how to use drugs, and greatly increase patients’ compliance with medication. It is critical for the management of medical big data in the future in China. In the future, we may develop artificial intelligence, machine learning and other means to standardize scoring.

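### The article sets out to confirm efficacy in some places and to explore it in others; with groups formed by choice and compliance and only recorded covariates matched, a significant difference cannot by itself confirm efficacy

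*Protocol article*

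**What the plan says.** **Aim.** Objectives {7}: "The objective of this trial is to confirm the efficacy and safety of butylphthalide on secondary prevention of stroke patients". Background {6a} gives the same strength of aim: "we designed this study to confirm the role of butylphthalide in secondary stroke prevention in the real world". The background paragraph of the Abstract says the same. The Discussion is weaker: "This trial will be exploring the efficacy and safety of butylphthalide in secondary prevention of ischemic stroke". The discussion paragraph of the Abstract uses the same weaker verb.

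**How the groups arise.** Trial design {8}: "Eligible participants will be assigned to the butylphthalide group or the control group according to their own wills". Sequence generation {16a} has "subjects assigned to this trial based on their actual conditions and wishes". Under Intervention measures, doctors plan medication according to the patient's condition and "recommend (rather than forcing) patients to take butylphthalide". Under Unblinding and allocation, the groups for analysis are fixed at the end of the study: good compliers form the butylphthalide group, with "patients without taking butylphthalide and patients with poor compliance as the control group". The comparator section {6b} agrees.

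**Analysis.** Statistical methods {20a} gives Kaplan–Meier curves, a log-rank test and a Cox model for recurrence, calls a two-sided P value of 0.05 or less statistically significant, and names one method against confounding: "Propensity score matching (PSM) is taken to ensure that the covariates are balanced and comparable".

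**Planned effect.** Sample size {14} assumes one-year recurrence falling from 17.7% to 14.7%, with 3168 per group for 90% power at two-sided 0.05, and 3727 per group after 15% dropout; 8000 patients are to be recruited.

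**The concern.** *Confirm* and *explore* are different strengths of conclusion, and the article does not say which one governs. The stronger verb stands in the Objectives, against which the result will be read.

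The design does not carry that verb. Patients who accept a recommended drug and then take it well for three months may differ from those who refuse it or take it poorly, in ways that also affect recurrence. Matching can balance what is recorded; it does not act on what is not. A P value measures sampling error, not this kind of bias, and a larger sample makes a biased difference more likely to be significant.

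At stake is the wording of the final claim. The Abstract says the trial is meant to widen the application of the capsules. A significant difference reported as confirmed efficacy would give that step more support than the comparison can provide.

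**Working it through.** **Inputs from the article (Sample size {14}).** Control risk 0.177; butylphthalide risk 0.147; two-sided alpha 0.05; power 90%; 3168 per group; 15% dropout; 8000 recruited.

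**Assumed inputs.** 3400 per group, which is 8000 × 0.85 / 2; this takes an equal split and no patients lost in matching. The strengths and prevalences of the unrecorded traits are illustrations only.

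**1. The plan's own figure.** Two-proportion formula, pooled variance, mean risk 0.162:

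n = [1.960·√(2 × 0.162 × 0.838) + 1.282·√(0.177 × 0.823 + 0.147 × 0.853)]² / 0.030² = 3168 after rounding up.

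3168 / 0.85 = 3727. Both stated figures are reproduced, so the sample-size arithmetic is not in question.

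**2. Planned effect and its E-value.** RR = 0.147 / 0.177 = 0.831; inverse 1.204.

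E = 1.204 + √(1.204 × 0.204) = 1.70.

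If the implied hazard ratio, ln(0.853) / ln(0.823) = 0.816, is treated as a risk ratio, E is 1.75.

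**3. Confidence limit.** At 3400 per group:

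SE(log RR) = √[0.823 / (0.177 × 3400) + 0.853 / (0.147 × 3400)] = 0.0554

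95% CI = 0.831 × exp(±1.960 × 0.0554) = 0.74 to 0.93 (upper limit 0.926, inverse 1.080)

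E for the upper limit = 1.080 + √(1.080 × 0.080) = 1.37 (1.36 at 3168 per group).

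**4. What an unrecorded trait does when the drug is inert.** Let the trait multiply recurrence risk by a, with prevalence t in the butylphthalide group and c in controls after matching:

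RR = [1 − t(1 − a)] / [1 − c(1 − a)]

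The last column is the chance of a significant apparent benefit with control risk 17.7% and 3400 per group.

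| a | t | c | RR | Chance of P≤0.05 |
|---|---|---|---|---|
| 0.5 | 60% | 30% | 0.70 / 0.85 = 0.82 | about 94% |
| 0.7 | 60% | 30% | 0.82 / 0.91 = 0.90 | about 49% |
| 0.5 | 50% | 40% | 0.75 / 0.80 = 0.94 | about 23% |
| 0.7 | 50% | 40% | 0.85 / 0.88 = 0.97 | about 10% |

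In the second row the expected butylphthalide risk is 15.95%, a difference of 1.75 points with z = 1.93, and a difference of exactly that size gives P = 0.054. The nominal chance of a false significant benefit is 2.5% in that direction.

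**5. Reading.** The E-value is a minimum, reached only at extreme prevalences. At more ordinary prevalences, a factor that doubles risk must be present in 56.5% of controls and 30% of the butylphthalide group to produce the whole planned effect. One that raises risk by half would need 77% against 30%. The factor required is therefore moderate, not slight.

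**The case against.** The best reply is that the article is open about being a non-randomised, real-world study, and that most of what can be said here applies to any such study. Four parts of it stand.

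- **Size.** A reader might infer from the E-value of 1.70 that any modest unmeasured factor would explain the whole planned effect. The table does not support that: it takes about a halving of risk and a 30-point gap that remains after matching. Nor does the sample make trivial differences significant; the threshold is about 1.8 points, against a planned difference of 3.
- **Recorded data.** Data management {19} lists demographic data, living habits and medical history, and sections {6b} and {11d} record other drugs. Part of what drives choice may therefore be available for matching. Ability to pay, frailty and health behaviour as drivers are assumptions.
- **Matching sentence.** It speaks of balanced covariates, not of comparable groups. Adding the word recorded would be an editorial improvement only.
- **Decision rule.** Nothing in the article equates P≤0.05 with confirmation. Section {20a} says only that such a result is statistically significant. That it would be reported as confirmed is an inference from joining that section to the Objectives.

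Sensitivity analyses may also be set out in a full protocol or analysis plan that is not shown, so their absence here is not the fault. What the reply does not remove is the conflict in the stated aim. A sensitivity analysis elsewhere would qualify the estimate without making these groups suitable for confirmation.

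**Conclusion.** The point holds as a mismatch between stated aim and design. The article says *confirm* in three places and *exploring* in two. With groups formed by choice and end-of-study compliance, and only recorded covariates matched, the weaker verb is the one the design supports.

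The planned RR of 0.83 could be produced entirely by a moderate unrecorded trait (E-value 1.70; 1.37 for the upper limit), and in the strongest assumed case an inert drug would give a significant result about 94% of the time. With weaker assumed traits that chance falls to about 49%, 23% or 10%. These figures rest on the planned rates, 3400 per group and prevalences that the documents do not give. They show that the bias could matter, not that it is present or that it would explain an observed effect.

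The correction is worth making because it costs little and governs how the main result is read.

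**What to change.** 1. In the Abstract background, Background {6a} and Objectives {7}, replace the aim of confirming with: estimate the association of butylphthalide use with stroke recurrence. This agrees with the exploratory wording of the Abstract discussion and the Discussion.
2. Prespecify that the primary hazard ratio is reported with a sensitivity analysis for unmeasured confounding. E-values for the estimate and for the confidence limit nearest 1 are one option.
3. State that P≤0.05 alone will not be reported as confirmed efficacy.

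The cost is a few changes of wording and a short calculation on the final estimate. The downside is a weaker headline claim. These changes do not repair the end-of-study reassignment of poor compliers to the control group, which is a separate defect and needs its own correction.
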